## Abstract

**Background:**

Gait retraining is a common therapeutic intervention that can alter gait characteristics to reduce knee loading in knee osteoarthritis populations. It can be enhanced when combined with biofeedback that provides real-time information about the users’ gait, either directly (i.e. knee moment feedback) or indirectly (i.e. gait pattern feedback). However, it is unknown which types of biofeedback are more effective at reducing knee loading, and also how the changes in gait affect pain during different activities of daily living. Therefore, this study aims to evaluate the acute (6 weeks of training) and chronic (1 month post training) effects of biofeedback based on personalised gait patterns to reduce knee loading and pain in people with knee osteoarthritis, as well as examine if more than one session of knee moment feedback is needed to optimise the gait patterns.

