This study will primarily explore the effectiveness of gait pattern feedback to reduce knee loading and knee pain during a 6-week gait retraining programme, and knee moment feedback group will be exploratory to identify the number of sessions needed to determine the optimal gait pattern over 6 weeks. In a long-term gait retraining programme, the gait patterns identified in the first session may not be optimal due to familiarisation with the environment, skin markers and desired gait alterations, as well as any learning effect or muscle activation adaptations [28]. Therefore, this study will explore if a participant’s optimal gait pattern changes or improves over time when provided with direct knee moment feedback, and how many sessions are required to identify a stable optimised gait pattern. Furthermore, there have not been any studies exploring the translative effect of gait retraining intervention into daily activities other than walking (e.g. sit-to-stand or stair climbing). Addressing these knowledge gaps in the literature will produce quantifiable outcome measures to identify and support the implementation of gait retraining for future clinical rehabilitation in KOA populations.

The primary objective of this study is to compare the effectiveness of gait pattern feedback to a control group, during a 6-week gait retraining programme in a KOA population. The secondary objectives are as follow:Explore the evolvement of gait patterns (FPA, step width and step length) when using knee moment biofeedback over time.Determine the optimal number of knee moment biofeedback sessions to identify the best combination of gait patterns (FPA, step width, step length) and quantify individual differences in the timescale for adaptation.Compare the similarity between gait pattern feedback and knee moment feedback to reduce KAM and pain.Explore and compare the successful internalisation of these two types of biofeedback gait retraining over time, through dual tasks, muscle activation and one-month gait retention.Explore the translative effect of these biofeedback gait retraining programmes on general daily activities.

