#### Biomechanical outcomes

Across all groups, we will collect the biomechanical outcomes measures listed below in all three assessment sessions (weeks 0, 6 and 9). In the intervention groups, we will collect all these measures during training sessions 1 and 6, while training sessions 2–5 will only record knee loading and gait pattern data (no muscle activation data). For the control group, all these measures will only be recorded during sessions 1 and 6.*Knee loading data* will be collected and calculated as KAM, KFM and KAM impulse. Hip moment will also be calculated as exploratory information.*Gait patterns data* will be collected as FPA, step width, and step length. Other gait parameter such as trunk lean and pelvis tilt will also be calculated.*Muscle activations data* will be measured by surface EMG from lower limb muscles using surface electrodes. Before placement, electrode locations on each participant’s affected leg will be palpated, shaved, lightly abraded, and cleaned with an alcohol swab. EMG normalisation will be performed using maximum voluntary contraction (MVC) tests for all these five muscle groups (knee extension, knee flexion, ankle plantar flexion, ankle dorsiflexion, hip abduction).

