### Biofeedback identification session

This session (Fig. 1) will only be conducted in the two intervention groups, and both intervention groups will receive knee moment feedback to identify their optimal gait patterns. Reflective markers and EMG electrodes will be attached. Participants will be instructed to walk on the instrumented treadmill and try various gait patterns (FPA, step width and step length), aiming to reduce the real-time knee moments graphs shown on the screen in front of them. They will first be instructed to try different FPAs, then try different step widths and finally different step lengths, to identify their optimal values for each gait parameter. Then, participants will be given 5 min to explore a combination of gait patterns that can consistently keep the knee moment graphs at a low level, in a symmetric, pain free and sustainable method. This 5-min period will be recorded to identify the FPA, step width and step length that most effectively reduces KAM for each individual.

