#### Gait pattern biofeedback gait retraining group

Real-time feedback of their live gait patterns (FPA, step width and step length) graphs with their personalised gait pattern target and their visual skeleton will be presented on the screen in front of the treadmill through the Visual 3D real-time plugin (C-Motion, Inc.) (Fig. 3). The participants individualised gait pattern target will depend on the outcomes from the identification session (week 0b, Fig. 1), which will be the same during each training session. Participants will be told to match the target as much as possible.

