### Statistical analysis

Study outcomes will be assessed quantitatively. The primary outcome will be KAM and KAM impulse, while NRS pain and WOMAC scores will be considered secondary. All other biomechanical outcomes (e.g. spee, EMG data, gait pattern variables) will become exploratory outcome variables in nature. The primary success of the trial will be based on a comparison of KAM reduction between week 0 and week 6, while the success of retention will be based on a comparison of between week 0 and week 10. In the knee moment feedback group, gait pattern changes (FPA, step width and step length) from week 1 to week 6 and 1-month follow-up will be compared to explore the evolvement of the gait pattern in response to knee moment feedback intervention. The proportion of participants adequately completing the programme and the average number of training sessions completed will be reported.

All outcomes will be analysed using the intention-to-treat approach and thus we will include data from all enrolled participants, regardless of dropout. Descriptive statistics will be used to compare participants randomised into the two intervention groups and a control group with respect to baseline variables. Continuous variables will be expressed as the means and standard deviations (if normally distributed). The data normality and sphericity will be tested using Shapiro–Wilk test and Mauchly’s test respectively. Linear mixed effect (LME) models will be used to evaluate whether knee loading variables, knee pain score and WOMAC score significantly differ between the three time points (week 0, week 6 and week 10), with group as fixed effect, and participant (repeat measures) as a random effect. LME will be used for our primary objective to explore the difference between baseline assessment (week 0) and post-intervention assessment (week 6) with comparison of gait pattern group and control group, and the secondary objective to explore the gait pattern difference across all time points in knee moment group. The example LME formula for comparison between the gait pattern and control group within MATLAB is stated as below:$${\text{glme}}\_\mathrm{KAM }=\mathrm{ fitglme}({\text{data}},\mathrm{ ^{\prime}}{\text{KAM}}1 \sim \mathrm{ Group }+\mathrm{ timepoint }+\mathrm{ timepoint}*\mathrm{Group }+ (1|{\text{Participant}})\mathrm{^{\prime}},\mathrm{ ^{\prime}}\mathrm{FitMethod^{\prime}},\mathrm{^{\prime}}\mathrm{Laplace^{\prime}})$$

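### The stated session-by-session analysis of the knee moment group tracks gait parameters only, so it cannot show whether later sessions found a better pattern

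*Protocol article*

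**What the plan says.** **The question.** The Abstract says the study will "examine if more than one session of knee moment feedback is needed to optimise the gait patterns". The Background asks whether a participant's "optimal gait pattern changes or improves over time when provided with direct knee moment feedback" and how many sessions give a stable optimised pattern. Its secondary objectives list the evolution of FPA, step width and step length first. A separate objective follows: "Determine the optimal number of knee moment biofeedback sessions to identify the best combination of gait patterns", together with individual differences in how long adaptation takes.

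**The criterion.** In the Biofeedback identification session, a recorded five-minute walk is used to find "the FPA, step width and step length that most effectively reduces KAM for each individual". The same section also wants the pattern to be symmetric, sustainable and free of pain. The section on the knee moment group sets a 10% reduction in first-peak KAM as the target, with a 1% limit on the rise in KFM.

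**The data.** Under Biomechanical outcomes, the feedback groups have knee loading and gait pattern data recorded in all six training sessions. Only muscle activation is dropped in sessions 2 to 5.

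**The analysis.** The Statistical analysis section describes the session-level work in the knee moment group twice. Once it is a comparison of FPA, step width and step length from week 1 to week 6 and at follow-up. Once it is the mixed model for "the secondary objective to explore the gait pattern difference across all time points in knee moment group". Knee loading variables are modelled at weeks 0, 6 and 10. A repeated measures Bland–Altman analysis is assigned to the similarity of the two feedback groups, with no variable or time points named.

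**The concern.** The objectives use two kinds of word. Evolvement and stable describe movement of the pattern, and the gait parameters measure that directly. Improves and best describe how good the pattern is, and the article ties that mainly to KAM. The only session-level outcomes it names are of the first kind.

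Three gait parameters feed one KAM value, so different combinations can give the same KAM. FPA, step width or step length may shift between sessions with no gain in KAM. KAM may also fall with little movement in any single parameter. Participants in this group aim for a target band, not a minimum, so they have room to move once inside it.

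At stake is the result that the Discussion part of the Abstract and the Conclusion both promise: how many knee moment sessions are needed. A report built only on the stated session-level outcomes could say when the pattern stopped moving. It could not say whether the sessions beyond the first bought any further reduction in knee loading.

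**Working it through.** The plan states no figure on this point, so there is none to reproduce. The check is mainly a comparison of what is asked, recorded and analysed.

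| Part of the question | Scale needed | Recorded by session? | Stated session-level analysis? |
|---|---|---|---|
| How the pattern evolves | FPA, step width, step length | Yes | Yes |
| When the pattern is stable | FPA, step width, step length | Yes | Yes, in effect |
| Whether a later pattern is better | KAM, with KFM and the target | Yes | None named |

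**Could the other knee loading analyses fill the last row?**
- The week 0, 6 and 10 models use the assessment weeks. Under Assessment sessions, walking is then overground at the participant's preferred gait. Two points during the programme (weeks 0 and 6) cannot show at which of sessions 1 to 6 the gain stopped.
- The primary model compares the gait pattern and control groups. It does not include the knee moment group.
- The Bland–Altman analysis may or may not use session KAM. Either way it addresses agreement between groups, not later against earlier sessions.
- The first knee moment session is the identification session in week 0b, but the stated comparison of gait patterns starts at week 1. A test of whether more than one session is needed has to include week 0b.

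**Illustration that pattern and KAM can part.** All values here are assumed; none comes from the article. Let D_w and D_l be a person's changes in step width and step length from session 1 to session 6, in arbitrary units, each with SD 0.8. Let

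KAM change = −D_w + D_l.

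The signs follow the Background, where wider and shorter steps reduce KAM. Take n = 20, and n = 16 after the article's 20% drop-out (20 × 0.8 = 16).

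*Case A: both drift upward by the same amount.* The mean KAM change is −drift + drift = 0. Share of 20,000 simulated trials with at least one parameter at p < 0.05:

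| Drift | n = 16 | n = 20 |
|---|---|---|
| 0.3 | 50% | 59% |
| 0.5 | 87% | 94% |
| 0.7 | 99% | 99.9% |

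The KAM test is significant in 5% throughout. Testing two parameters explains only part of this. With no drift the chance of at least one is 1 − 0.95² = 0.0975, and with a Bonferroni correction the range is still 35% to 97% (n = 16) and 44% to 99% (n = 20).

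*Case B: step length moves the other way, so both changes lower KAM.* At drift 0.5 and n = 20, the mean KAM change is −0.5 − 0.5 = −1.0 and its SD is 0.8 × √2 = 1.13. The KAM test is significant in 96% of trials and at least one parameter in 94%.

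The gait-parameter result at drift 0.5 and n = 20 is 94% in both cases, while the truth about KAM is opposite. The parameters alone therefore cannot tell the two cases apart.

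**The case against.** The strongest reply is that the quoted model serves the objective on evolution, for which FPA, step width and step length are the right outcomes. The Statistical analysis section links the gait pattern comparison to evolvement and nowhere says that it settles the number of sessions. On that view the article simply gives no analysis for the latter objective, which a fuller document may supply. The first part stands, and the gait parameters should stay. The second stands only in part: the article does commit to session-level outcomes for this group, and they leave out the one it uses to choose a pattern.

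A reader might infer that the plan will report drift as further optimisation, or that it judges later patterns by gait parameters alone. No sentence says so. Stability, which the Background also asks about, is properly read from those parameters.

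It is also fair that optimal is not KAM alone. KFM, symmetry, pain and sustainability enter, and the target is a 10% reduction, not the lowest possible value. A participant who reaches the target early may hold it by design, so flat KAM does not by itself prove that later sessions added nothing. The fix has to allow for this.

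The simulation is open to the charge that KAM cancels by construction in Case A. It does, and that case has participants lengthening their steps while watching live KAM and trying to lower it. Case B shows agreement under equally arbitrary assumptions.

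Lastly, a reader might say that the plan overlooks a randomised answer, since the gait pattern group keeps its identification-session target, "which will be the same during each training session". That goes too far. The article already lists the comparison of the two feedback groups on KAM and pain as exploratory. The contrast also mixes number of sessions with feedback type and target rule. With 80% power it detects only a standardised difference of about 0.91 (20 v 20) or 1.02 (16 v 16).

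**Conclusion.** The point holds in a limited form. The session-level outcomes stated for the knee moment group fit evolution and stability, but they cannot show that a later pattern is better. The stated knee loading models cannot show at which session KAM stopped improving. This rests on the text alone.

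No numerical size can be given. The simulated percentages depend on assumed drifts, SDs and effects on KAM, and they show only that drift without KAM gain is possible, not that it is likely. It would be wrong to infer that KAM in this group goes unanalysed, since it is modelled at weeks 0, 6 and 10.

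The knee moment group is exploratory and the primary comparison of gait pattern feedback with control is unaffected. The change is still worth making, because the number of sessions is the purpose the Background gives for this group of 20, and the data are already planned.

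**What to change.** In the Statistical analysis section:

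- Add treadmill first-peak KAM by session in the knee moment group (the recorded week 0b period and sessions 1 to 6) as a co-outcome for the number-of-sessions objective.
- Report it with KFM and attainment of the target already set for this group, for the group and for each individual, since the objective asks about individual timescales.
- Conclude that later sessions improved the pattern only if KAM is lower than with the pattern first identified, or the target is newly met, without breaching the stated KFM limit.
- Keep FPA, step width and step length to describe how the pattern evolved and when it became stable.
- If session KAM is compared between the knee moment and gait pattern groups, label it exploratory and say that feedback type and target rule differ between them.

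The cost is wording and a little extra exploratory analysis. Training-session knee loading is already collected and the week 0b period is already recorded, so participants carry no added burden.

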## Methods

### Study design

This is a parallel group, randomised controlled trial, where participants will be randomly allocated into three groups; knee moment biofeedback group, gait pattern biofeedback group and control group. In participants with bilateral KOA, the most painful knee will be studied. The primary outcome will be KAM, while knee pain and functional ability will be considered secondary. All other outcomes will be exploratory outcome variables. The primary comparison will be between gait pattern feedback group and control group, while the comparison between gait pattern feedback group and knee moment feedback group will be exploratory.

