### Study population/sample size

A sample size calculation was performed based on randomisation with stratification. Using an alpha level of 0.05, a power of 0.8, and an effect size estimates of 1.01 for KAM based on a previous gait retraining study with a similar design compared to our primary comparison (gait pattern group vs control group) [22]. Given that the comparison between gait pattern group and knee moment group is a secondary objective and no study has done the similar design, we will stick with the sample size needed for our primary objective. Seventeen participants are required for each experimental group. Thus, a total of thirty-four participants are needed to adequately power the study and detect significant differences in KAM between groups. Using a conservative estimate of twenty percent drop-out rate, the aim is to recruit twenty participants per group. For control group, we used an allocation ratio of 2:1 requiring recruitment of ten participants. This unequal allocation ratio for control group has been shown to increase the amount of data in the intervention groups where individual responses are likely more variable [30, 31]. In total, this study will recruit fifty participants.

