### Randomisation

After the baseline assessment, participants will be randomly allocated (2:2:1) to the knee moment biofeedback group, gait pattern biofeedback group or control group, using a block randomisation plan by the researcher. Blinding is not achievable in this intervention study, and therefore neither participants nor researcher will be blinded.

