### Assessment sessions

There will be three assessment sessions (Fig. 1) throughout the programme (week 0, 6 and 10). All three assessment sessions will be identical, except the Oxford Knee Score assessment will be performed in the baseline assessment session (week 0). The WOMAC questionnaire will be assessed at the beginning of each assessment session, after which, reflective markers and EMG electrodes will be attached to the participant. Overground walking, stair ascent and descent, and sit-to-stand will be performed in a block randomised order. All activities will be performed under their preferred overground gait condition, and each activity will be repeated five times. The overground walking speed during each assessment session will be controlled to be within 20% of the baseline overground walking speed. At the end of the final trial of each activity, participants will be asked to report their perceived knee joint pain using NRS.

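### The printed primary model is fitted by maximum likelihood with free baseline means: the standard error is slightly too small at 24–30 participants under equal variances, and precision from baseline KAM is left unused

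*Protocol article*

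**What the plan says.** The Study design section fixes the contrast: "The primary comparison will be between gait pattern feedback group and control group". The Statistical analysis section then gives one model for it: "The example LME formula for comparison between the gait pattern and control group within MATLAB is stated as below". The call is fitglme with first-peak KAM as response; group, time point and their interaction as fixed effects; a random intercept per participant; and Laplace as the fit method. The time points are baseline and post-training. No distribution is named, but the text calls the model a linear mixed-effects model.

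On order of events, the Randomisation section says "After the baseline assessment, participants will be randomly allocated (2:2:1" across the three arms. On numbers, the sample-size section says "Seventeen participants are required for each experimental group", then "Using a conservative estimate of twenty percent drop-out rate, the aim is to recruit twenty participants per group", and for the comparator "For control group, we used an allocation ratio of 2:1 requiring recruitment of ten participants". It justifies the unequal allocation by expecting more variable individual responses in the intervention groups. Under Assessment sessions, "each activity will be repeated five times".

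**The concern.** Two separate features of the printed call deserve attention.

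**Estimation.** For a continuous, normally distributed outcome with identity link, the Laplace approximation is exact, so the fit is ordinary maximum likelihood. Maximum likelihood divides the residual variance by the number of participants without subtracting the fixed effects estimated. In large trials this is negligible. Here the comparison has 30 participants, or 24 after the planned dropout.

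**Baseline.** The group main effect lets the arms have different true means at baseline. Because allocation happens after the baseline assessment, those means are equal in expectation by design. A model that does not use this estimates the plain difference in mean change, which is generally less precise than a baseline-adjusted difference.

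At stake are the accuracy of the primary p-value and interval, and precision in a comparison with few controls.

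**Working it through.** **Inputs.** Alpha 0.05, power 0.8 and standardised effect 1.01, from the sample-size section ("Using an alpha level of 0.05, a power of 0.8, and an effect size estimates of 1.01 for KAM"). Arms of 20 and 10; after 20% dropout, 20 × 0.8 = 16 and 10 × 0.8 = 8. So N = 30 or N = 24. Assumptions for step 2: normal outcome, identity link, one value per participant per visit, complete pairs, equal variances.

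**1. The plan's own figure.** A two-sided two-sample t-test at effect 1.01 needs 17 per group (power 81.5%), which matches the plan. The same test has power 71% at 20 versus 10 and 61% at 16 versus 8.

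**2. Maximum likelihood.** With two time points and a random intercept, the interaction is the difference between arms in mean change. Maximum likelihood divides its variance by N, REML by N − 2, so SE(ML)/SE(REML) = √((N − 2)/N).
- N = 30: √(28/30) = 0.966, so 3.4% too small.
- N = 24: √(22/24) = 0.957, so 4.3% too small.

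A fitted mixed model at N = 30 reproduced 0.966. True two-sided type I error is 2·P(t on N − 2 df > critical value × ratio):

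| Reference distribution | N = 30 | N = 24 |
|---|---|---|
| t, N − 2 df | 5.8% | 6.0% |
| t, 2N − 4 df (observation level) | 6.3% | 6.7% |
| normal | 6.9% | 7.4% |

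In 100,000 simulated trials per setting the results were close to these, and REML with N − 2 df gave 5.0–5.1%.

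**3. Unequal variances.** Let the change SD in the intervention arm be k times that in control. The true variance is k²/20 + 1/10; the pooled model expects ((19k² + 9)/28) × (1/20 + 1/10). At k = 1.25 (assumed), these are 0.178 and 0.207, so the pooled SE is √(0.207/0.178) = 1.08 times the true one. Multiplied by 0.966 this gives 1.04: the maximum-likelihood SE is now about 4% too large. Simulated type I error with 2N − 4 df:

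| k (assumed) | 20 vs 10 | 16 vs 8 |
|---|---|---|
| 1.1 | 5.4% | 5.9% |
| 1.25 | 4.7% | about 5% |
| 1.5 | 3.6% | 3.9% |

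**4. Baseline adjustment.** With equal visit variances and correlation rho, the variance of ANCOVA relative to change score is (1 − rho²)/(2(1 − rho)) = (1 + rho)/2.

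| rho (assumed) | Variance ratio | SE reduction |
|---|---|---|
| 0.5 | 0.75 | 13% |
| 0.7 | 0.85 | 8% |
| 0.8 | 0.90 | 5% |
| 0.9 | 0.95 | 2.5% |

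Simulated gains, which include the cost of estimating the slope, were 11–13% of the SE at rho 0.5 and about 3% at rho 0.8. If 1.01 is on the scale of the change-score SD (the documents do not say), approximate power rises from 71% to 73–83% at 20 versus 10, and from 61% to 63–73% at 16 versus 8, for rho 0.9–0.5.

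**5. Does the form of adjustment matter?** Take rho 0.7, baseline SD 1 and week-6 SD 1.25 in both arms (assumed). The covariance is 0.7 × 1.25 = 0.875. Variances per unit:
- Change score: 1 + 1.5625 − 2 × 0.875 = 0.813.
- ANCOVA: 1.5625 × (1 − 0.49) = 0.797.
- Random intercept with baseline means constrained equal: the implied slope is 0.875/1.28125 = 0.683, giving 1.5625 + 0.683² − 2 × 0.683 × 0.875 = 0.834.

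So constraining the baseline while keeping only a random intercept can do worse than the printed model. ANCOVA does not, asymptotically, under a common within-arm covariance.

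**The case against.** The strongest reply has four parts.

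**The formula is labelled an example, and an unseen analysis plan may settle degrees of freedom and adjustment.** This limits the point but does not remove it. The estimator and the fixed effects are stated in print for the primary comparison. The degrees of freedom are not, which is why a range is given rather than one figure.

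**A difference in change is what the plan says it wants.** The trial's success is defined by comparing KAM reduction from week 0 to week 6, and the change-score contrast is unbiased under randomisation. This stands: baseline adjustment is a gain in efficiency and not the correction of a bias.

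**The direction of the error is not established.** This also stands. A reader might infer that the primary p-value and interval are definitely too optimistic. The documents do not support that, because the plan itself expects more variable responses in the larger arm, and step 3 shows that a modest excess cancels or reverses the inflation.

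**The baseline is already in the model.** Correct. A reader might infer that baseline KAM is wasted, but it enters as a response row. Only the part of its information that ANCOVA would recover is lost, and that part is small when rho is high. Nor does the free group term cause the understated SE; that comes from maximum likelihood and the degrees of freedom.

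A reader might also infer, from the five repetitions per activity, that repeated trials will be entered as separate rows and treated as independent within participant, with much larger error inflation. Nothing in the documents says the data will be laid out that way, so no weight is put on it.

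**Conclusion.** The point holds in a limited form. Under a normal outcome, equal variances, complete pairs and one value per participant per visit, the printed fit understates the standard error by 3.4% (20 versus 10) to 4.3% (16 versus 8). Type I error is then roughly 6–7% instead of 5%. The sign of this error depends on the variance ratio between arms, which the documents do not give.

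Independently, the model forgoes a variance reduction of 5–25% for rho 0.9–0.5, given equal visit variances. Neither effect is large, and neither invalidates the trial. Both concern a method the plan states, and both can be improved without new data in a comparison with at most ten controls.

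**What to change.** Before outcomes are analysed, state the primary analysis as an ANCOVA: week-6 first-peak KAM regressed on baseline first-peak KAM and group, using each participant's mean over the trials at a visit. Base inference on the t distribution with residual degrees of freedom, and report the adjusted difference with its 95% confidence interval.

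If a mixed model is kept, fit it with fitlme by REML with Satterthwaite degrees of freedom. If baseline means are constrained to be equal, allow an unstructured covariance over the two visits instead of a random intercept alone (step 5).

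The cost is a few lines of code and wording. REML intervals are slightly wider, and the covariate takes one degree of freedom. ANCOVA uses only participants measured at both visits, so the text should say how it fits the intention-to-treat statement; the constrained mixed model keeps those with baseline only. Both options still pool the variance across arms, so neither removes the effect shown in step 3.

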Where KAM1 is the1st peak KAM; Group is the gait pattern group and control group; Timepoints includes baseline and post-training.

Repeated measures Bland–Altman analysis will be used to test the similarity between gait pattern group and knee moment group [35].

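### Bland–Altman limits of agreement need both programmes measured in the same people, so they cannot show whether two independent randomised groups respond similarly

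*Protocol article*

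**What the plan says.** The last sentence of Statistical analysis reads: "Repeated measures Bland–Altman analysis will be used to test the similarity between gait pattern group and knee moment group". It serves one of the secondary objectives listed in Background: "Compare the similarity between gait pattern feedback and knee moment feedback to reduce KAM and pain".

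The design is given in Study design: "This is a parallel group, randomised controlled trial, where participants will be randomly allocated into three groups". Randomisation adds that "participants will be randomly allocated (2:2:1) to the knee moment biofeedback group, gait pattern biofeedback group or control group". No crossover and no matching of participants is described.

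Study design also sets the status of this contrast: "the comparison between gait pattern feedback group and knee moment feedback group will be exploratory". The Conclusion again calls it an exploratory objective.

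Statistical analysis also plans linear mixed models for knee loading, pain and WOMAC over weeks 0, 6 and 10, with group as a fixed effect. The uses it names are gait pattern versus control, and change over time within the knee moment group. The printed example formula restricts Group to gait pattern and control. Bland–Altman is the only method named for similarity between the two feedback groups.

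**The concern.** Bland–Altman analysis asks how far two measurements of the same person differ. The repeated-measures form allows several such pairs per person, but each pair must still come from one person under both methods. Here each participant follows one programme. Assessments at weeks 0, 6 and 10 repeat within a person and do not link people across arms.

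The similarity question has practical weight in the protocol's own argument. Background says that knee loading feedback cannot at present be given outside a laboratory, and that gait pattern feedback is more feasible in clinic and home settings. The Conclusion looks to the results for clinical guidance and for portable devices. Wide limits of agreement could be read as showing that the programmes differ, when they show only that people differ from one another.

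**Working it through.** **Inputs.** Two independent arms of 20 (Study population/sample size; Randomisation), or 16 per arm if 20% are lost (20 × 0.8). The common SD of the analysed outcome is set to 1, because the article gives no SD. It gives no similarity margin either.

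**The plan's own figure.** No number is stated for the similarity analysis. The sample size belongs to the primary comparison: "Using an alpha level of 0.05, a power of 0.8, and an effect size estimates of 1.01 for KAM", leading to "Seventeen participants are required for each experimental group". A two-sided t test with 1:1 groups has power 0.789 at 16 per group and 0.815 at 17, so 17 is reproduced. The section says this number is reused for the feedback comparison, which has no calculation of its own.

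**Is there a hidden pairing?** The one shared exposure is the week 0b session, where "both intervention groups will receive knee moment feedback to identify their optimal gait patterns". It sets gait targets. It does not give anyone an outcome under both six-week programmes.

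**What the limits would estimate.** Pair a person from one arm with an unrelated person from the other. Let the true difference between programmes be δ.
- Variance of the difference: 1 + 1 = 2.
- Limits: δ ± 1.96 × √2 = δ ± 2.77 SD.
- δ moves the centre and has no effect on the width.

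Simulation at 20 v 20 (5,000 runs each) gave mean half-widths of 2.73, 2.74 and 2.73 SD for δ = 0, 0.5 and 1.01. For contrast, genuine within-person pairs with correlation ρ give 1.96 × √(2(1 − ρ)): 1.52 SD at ρ = 0.7 and 0.88 SD at ρ = 0.9. Independent arms have no such correlation to use.

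**Dependence on the pairing.** One simulated 20 v 20 data set was re-paired 20,000 times:

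| Quantity | Result |
|---|---|
| Mean difference | 0.07 SD in every re-pairing |
| Half-width of limits, full range | 1.71 to 3.35 SD |
| Half-width of limits, central 95% | 2.12 to 3.07 SD |

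**What a valid comparison delivers.** The 95% CI half-width for a simple unadjusted difference in means is t(0.975, 2n − 2) × √(2/n).
- n = 20: 2.024 × 0.316 = 0.64 SD.
- n = 16: 2.042 × 0.354 = 0.72 SD.

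The matching 90% CI half-widths are 0.53 and 0.60 SD.

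**What an equivalence claim would need.** The margins here are assumptions. For two one-sided tests at 0.05, 80% power and zero true difference, n per group = 2 × ((1.645 + 1.282)/margin)².

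| Assumed margin (SD) | n per group |
|---|---|
| 0.25 | 275 |
| 0.50 | 69 |
| 0.75 | 31 |
| 1.01 | 17 |

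**The case against.** **The comparison is exploratory.** The protocol says so twice and does not size the trial for it. Primary success rests on KAM from week 0 to week 6, gait pattern versus control, by mixed model. This stands, and it limits the severity.

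**Part of the output is sound.** A reader might infer that everything the analysis produces depends on how rows are matched. That is not so. With equal, complete arms the mean difference equals the difference in group means under every pairing. If dropout leaves the arms unequal, it would also depend on who is left unpaired. The fault lies in the limits.

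**The numerical harm can be overstated.** It is tempting to set 2.77 SD against 0.64 SD as the loss from using the wrong method. These are different quantities: one describes spread between individuals, the other uncertainty in a mean. Like for like, a CI on the Bland–Altman mean difference at n = 20 has an expected half-width of about t(0.975, 19) × √(2/20) = 2.093 × 0.316 = 0.66 SD, close to 0.64 SD.

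**A usable model is nearly there.** The general mixed model covers three time points with group as a fixed effect, and Overview of the programme limits the week 10 visit to the two intervention groups. The article does not assign that model to the similarity objective, but a reader should not infer that the whole analysis section is unable to address it.

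**The cited variant is not visible.** Its exact implementation is unknown. This is a reason not to say how pairs would be formed; it does not supply pairs that the design lacks.

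**Conclusion.** The point holds: the stated method does not fit the stated design. Limits of agreement between these two arms would average about ±2.77 SD whether or not the programmes have the same effect, and they would vary with an arbitrary pairing. They therefore cannot show similarity for KAM or pain. This is a named method that cannot do its job, not a detail left to a fuller document.

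The figures assume a common SD, independent participants and approximate normality. The equivalence sample sizes also rest on margins that the article does not give. They show how much the sample size can support and do not measure the Bland–Altman error.

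The consequence is confined to one secondary objective with exploratory status. A reader might infer that the trial's main conclusion is at risk; the documents do not support that, because the gait pattern versus control analysis uses a different method. This is a change that should be made.

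**What to change.** Replace the Bland–Altman sentence. Estimate the gait pattern minus knee moment difference in change in KAM and in NRS pain at week 6 and at week 10. Use the group-by-time mixed model form already in Statistical analysis, with Group set to the two feedback arms and weeks 0, 6 and 10 as time points. Report each difference with its 95% CI, descriptively and labelled exploratory.

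A formal equivalence test is optional. If the authors want to conclude that the programmes are similar, they should state a margin and its justification before the data are seen, and conclude similarity only if the 90% CI lies inside it. Without a margin, they should make no similarity claim.

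The cost is a few lines of analysis text. Both feedback arms already attend weeks 0, 6 and 10, so no new data are needed. The downside is a plain admission that 16 to 20 per arm is unlikely to show similarity within a tight margin: even an observed difference of zero would carry a 90% CI of roughly ±0.53 to ±0.60 SD.
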